### Sample Size

A previous study that included physiotherapy as an intervention reported a mean VAS score for back pain of 3.05 (SD 1.36) points after treatment [11]. This was considered to anticipate an improvement of at least 2.79 points after *marma* therapy. Assuming a between-group difference of 1 point, with 80% power at 5% level of significance, the derived sample size was 72 participants. Furthermore, assuming a 20% attrition rate, the final sample size for this study was 90 participants, randomly allocated to the 2 groups in a 1:1 ratio (n=45, 50% participants per group). The effect size will be determined after the data analysis is completed.

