### Outcome Measures

The primary outcome of this study is a reduction in pain intensity in the lumbosacral region and legs (radiating pain) perceived by participants, assessed as the change in the 10 cm VAS score at day 30 and after 3 months from baseline.

The secondary outcomes of this study are improvement in functional disability due to LDH, assessed by the ODI, version 2.0; change in neurodynamic evaluation, assessed using the SLRT; improvement in QoL, assessed by the SF-36; comparison of dependence on allopathic analgesics; and assessment of safety and acceptability of the *marma* therapy in patients with LDH, assessed by the incidence of adverse events (AEs) associated with the therapy and compliance of patients to *marma* therapy.

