### Data Analysis

After verification for accuracy, all collected data will be anonymized prior to statistical analysis. All analyses will follow both the intention-to-treat and per-protocol principles to evaluate the robustness and sensitivity of the results. Any missing or incomplete responses will be addressed through Bayesian imputation. To make the imputation robust, regression-based imputation will also be applied if sufficient information is available in the data. Furthermore, the data will be used for descriptive analysis. Categorical variables will be described as frequencies and percentages, while continuous variables will be summarized as mean (SD) or median (IQR), depending on the distribution of the data (normal or skewed). Inferential analyses will be performed after descriptive analysis of the data. For within-group comparisons, data will be analyzed using the paired 2-tailed t test or the Wilcoxon signed-rank test, depending on the distribution of the data for pre-post observations. Between-group comparisons will be performed using the independent-samples *t* test or Mann-Whitney *U* test, depending on the normality of the data.

Repeated-measures ANOVA or the Friedman test will be used for within-group and between-group analyses of the outcomes assessed at multiple time points. The generalized estimating equation and the repeated-measures ANOVA, along with factor analysis, will also be performed if any confounding factors are found during the analysis. Analysis of covariance will be performed if baseline differences between groups are observed. A 2-sided significance level of 5% will be considered for all analyses. All statistical analyses will be performed using Stata software (version 16.1; StataCorp).

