## Results

Participant recruitment was initiated on April 4, 2022, and as of November 2025, a total of 90 patients have been enrolled. Of these, 70 (77.8%) study participants have completed the final follow-up. Data cleaning is now complete, and the results will be published once the analysis is complete. The final report and data interpretation are expected to be submitted for publication in 2026.

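### The sample size of 72 does not follow from the inputs given for it, which yield 60 to 62, and the SD used is not shown to fit the change-from-baseline primary outcome

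*Protocol article*

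**What the plan says.** The Sample Size section takes its only SD from an earlier physiotherapy study, which "reported a mean VAS score for back pain of 3.05 (SD 1.36) points after treatment". It says that this result was used to "anticipate an improvement of at least 2.79 points after" marma therapy. The calculation itself is one sentence: "Assuming a between-group difference of 1 point, with 80% power at 5% level of significance, the derived sample size was 72 participants". Attrition of 20% then raises the total to 90, or 45 per group.

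Two other sections bear on this. Data Analysis fixes sidedness: "A 2-sided significance level of 5% will be considered for all analyses". Outcome Measures defines the primary outcome as pain in the lumbosacral region and legs, "assessed as the change in the 10 cm VAS score at day 30 and after 3 months from baseline". Neither an SD for that change nor a correlation between baseline and follow-up scores is given.

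**The concern.** The section presents a complete derivation, with difference, SD, power, level, allocation and result, but the result is not what those inputs produce. Two further links are missing. A post-treatment mean of 3.05 implies no improvement unless a baseline is known, and none is given. Nor is there a control-arm improvement that would connect 2.79 to the 1-point difference. Finally, the SD belongs to a single score for back pain after treatment, while the primary comparison concerns a change score covering leg pain as well.

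What is at stake is interpretation. If the trial shows no difference, readers will want to know what it could have detected on its primary outcome, and the section does not tell them.

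**Working it through.** **Inputs.** Difference 1 point, SD 1.36, power 80%, 1:1 allocation and 20% attrition (Sample Size); two-sided 5% (Data Analysis).

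**1. Can 72 be reproduced?** For two means, n per arm = 2 × (z₀.₉₇₅ + z₀.₈₀)² × SD² / difference².

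- (1.960 + 0.842)² = 7.849
- n = 2 × 7.849 × 1.36² / 1² = 29.03, so 30 per arm, **60** in total
- Exact (noncentral t): 30.03, so 31 per arm, **62** in total

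The stated 72 is not reproduced. The next step is: 72 / (1 − 0.20) = 90. The same step would give 75 from 60, or 78 from 62.

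**2. Power of 72 on the stated inputs.** At 36 per arm with difference 1 and SD 1.36, power is 87% (t test; 88% by the normal approximation).

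**3. What would give 72?** Each of these routes needs an input that the article does not state:

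| Route | Calculation | Result |
|---|---|---|
| Larger SD | √(36 / (2 × 7.849)) | SD 1.51 (1.49 by exact t) |
| Smaller difference | 1.36 × 2.802 × √(2/36) | 0.90 point |
| Alpha 0.025 for two time points | 2 × (2.241 + 0.842)² × 1.36² = 35.16 | 36 per arm (normal approximation only; exact t gives 36.4) |
| Attrition already added | 60 × 1.2 | 72, but attrition would then be counted twice |

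Changing the power or sidedness does not help. At 85% power the total is 68 to 70, at 90% it is 78 to 80, and a one-sided test at 80% needs 46 to 48. Inflating for the Mann-Whitney test gives 62 to 70, depending on the factor.

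**4. From the post-treatment score to the change score.** Assume, since the article does not say, that the SD is 1.36 at both baseline and follow-up, with correlation ρ between them. Then SD of change = 1.36 × √(2(1 − ρ)). The t-test power for a 1-point difference at 36 per arm is:

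| ρ (assumed) | SD of change | Power |
|---|---|---|
| 0.2 | 1.72 | 68% |
| 0.3 | 1.61 | 74% |
| 0.4 | 1.49 | 80% |
| 0.5 | 1.36 | 87% |
| 0.6 | 1.22 | 93% |
| 0.7 | 1.05 | 98% |

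Power is therefore above or below 80% according to whether the correlation is above or below about 0.4. The documents do not give it.

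**The case against.** The strongest reply is that the error is harmless: on the article's own difference and SD, 72 is more than enough. That stands. A reader might infer that the 80% figure has no basis, or that the trial is underpowered, and the documents support neither. Under randomization the expected difference in post-treatment means equals the expected difference in changes, so the 1-point difference carries over to the primary outcome. The post-treatment SD is an imperfect proxy, and it equals the change SD when the variances are equal and the correlation is 0.5. Quoting only low correlations would make the case look worse than it is.

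A second reply is that the article condenses a fuller protocol, where the missing input may stand. It may, and for that reason an SD of about 1.5 should not be presented as the explanation; it is one route among several. But the article does more than omit a detail. It gives a set of inputs and a result that disagree, and it states the level as 5%.

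A reader might also make much of the completion figure, "70 (77.8%) study participants have completed the final follow-up", which is a 22.2% loss against the planned 20% and two short of 72. This carries little weight. With an even split, which is assumed because no counts by arm are given, power at SD 1.36 falls only from 86.8% at 36 per arm to 85.8% at 35. The count refers to the final visit, whereas day 30 is also a primary time point. The plan also includes an intention-to-treat analysis with imputation.

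**Conclusion.** The point holds as an error in the reported derivation. The stated inputs need 60 to 62 evaluable participants, not 72, and 72 gives about 87% power on them. The 2.79-point improvement cannot be linked to the mean of 3.05 or to the 1-point difference.

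Power for the primary outcome cannot be verified, because no SD for the change is given. The range of 68% to 98% rests on assumed correlations of 0.2 to 0.7 and on equal SDs of 1.36 at both times; it shows how much depends on the missing figure and is no estimate of the trial's actual power. The size of the trial is not shown to be inadequate.

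**What to change.** Correct the Sample Size section in three places.

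1. State the SD, alpha, test and time point actually used to obtain 72. If they are those now printed, say instead that they require 60 to 62 evaluable participants and that 72 gives about 87% power. An SD should not be worked backwards to fit 72.
2. Derive the 2.79-point improvement from a stated baseline and control-arm improvement, or remove it.
3. Say that 1.36 is a post-treatment SD for back pain used as a proxy for the change in back and leg pain, and give power over a stated range of change SDs. Tying it to a baseline-adjusted comparison would not match the plan, since Data Analysis reserves analysis of covariance for the case where baseline differences are observed.

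The cost is some rewording and one recalculation. The 90 participants are already enrolled and no change in enrolment follows; the final report is still to be submitted, so the corrected figures can appear there. For some change SDs the restated power will fall below 80%.

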### Recruitment and Participant Flow

After receiving approval from the Institutional Ethics Committee (IEC) and registering the study with the Clinical Trial Registry of India, all medical and paramedical staff are sensitized to the trial and its eligibility criteria. Patients presenting with concerns related to LBP and associated radiating pain in the lower limb in the OPDs of various departments of the hospital are referred to a special OPD for thorough assessment. Participants are recruited for the study based on the defined inclusion and exclusion criteria. A medical professional and a physiotherapist are delegated the responsibility to screen the patients clinically and get the tests conducted for the patients willing to participate and found to be eligible. Sensitization camps are conducted in nearby areas to create awareness regarding the project at the study site.

### Assignment of Interventions

The participants are randomized to 2 study groups in the ratio of 1:1. SPSS (version 15.0; IBM Corp) is used to generate the random number sequence. Allocation concealment is ensured by using the sequentially numbered, opaque, sealed envelope technique. The sequence of randomization and preparation of the sealed envelope technique is done centrally by the biostatistics unit at the sponsor’s headquarters. The envelopes are opened by the study participants after completion of the baseline assessment, and the intervention is given to them as per the group allocation. Both the participant and the investigator are aware of the group allocation at the end of the baseline assessment. This trial is an open-label study. However, the research personnel assessing the primary outcome and the secondary outcomes, namely, functional disability and neurodynamic evaluation, were not aware of the group to which participants were allocated.

### Data Collection and Management

After screening patients, the eligible participants are included in the study, and data are collected in a case record form (CRF). The data are subsequently recorded as an electronic CRF (e-CRF) on the same day. The CRF is prepared with appropriate coding to be entered into the e-CRF. Periodic data cleaning is performed to ensure the accuracy of the data entered in the e-CRF. The CRFs are stored in a secure location with restricted access.

Before initiating the study, the project team, including the investigators, is trained by the sponsor regarding the study protocol, standard operating procedures for data collection, various assessments, and Good Clinical Practice guidelines. The study participants are informed in detail about the study procedures and follow-up timelines before screening, as well as at the end of the baseline period, before the intervention begins, to confirm their consent for participation in the trial. To minimize loss to follow-up, the study team sends reminder calls and messages to participants 1 to 2 days prior to their scheduled visits.

### Data Analysis

After verification for accuracy, all collected data will be anonymized prior to statistical analysis. All analyses will follow both the intention-to-treat and per-protocol principles to evaluate the robustness and sensitivity of the results. Any missing or incomplete responses will be addressed through Bayesian imputation. To make the imputation robust, regression-based imputation will also be applied if sufficient information is available in the data. Furthermore, the data will be used for descriptive analysis. Categorical variables will be described as frequencies and percentages, while continuous variables will be summarized as mean (SD) or median (IQR), depending on the distribution of the data (normal or skewed). Inferential analyses will be performed after descriptive analysis of the data. For within-group comparisons, data will be analyzed using the paired 2-tailed t test or the Wilcoxon signed-rank test, depending on the distribution of the data for pre-post observations. Between-group comparisons will be performed using the independent-samples *t* test or Mann-Whitney *U* test, depending on the normality of the data.

Repeated-measures ANOVA or the Friedman test will be used for within-group and between-group analyses of the outcomes assessed at multiple time points. The generalized estimating equation and the repeated-measures ANOVA, along with factor analysis, will also be performed if any confounding factors are found during the analysis. Analysis of covariance will be performed if baseline differences between groups are observed. A 2-sided significance level of 5% will be considered for all analyses. All statistical analyses will be performed using Stata software (version 16.1; StataCorp).

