*Trayodashanga guggulu* tablets, weighing 500 mg each, are given as oral medication to the study participants in both groups at a dose of 1 g thrice daily, 2 hours after meals, with lukewarm water for 3 months. Participants are allowed to take oral analgesics as rescue medication for pain relief upon telephonic consultation with the investigator. Ongoing medications reported at baseline for any chronic condition (not mentioned in the exclusion criteria) are also continued by the study participants as concomitant medication. Participants who are unwilling to continue, are noncompliant with the study procedure, or meet any exclusion criteria during the study period are withdrawn from the study.

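### Regression-based imputation cannot show that the Bayesian imputation is robust to pain-related dropout, because in standard form both assume missing at random

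*Protocol article*

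**What the plan says.** All statements are in the protocol article.

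- **Data Analysis, first method:** "Any missing or incomplete responses will be addressed through Bayesian imputation".
- **Data Analysis, second method:** "To make the imputation robust, regression-based imputation will also be applied if sufficient information is available in the data". The section gives no missingness assumption for either method and does not say whether the regression imputation is single or multiple.
- **Data Analysis, analysis sets:** "All analyses will follow both the intention-to-treat and per-protocol principles to evaluate the robustness and sensitivity of the results".
- **Results:** "Of these, 70 (77.8%) study participants have completed the final follow-up". The same section adds: "Data cleaning is now complete, and the results will be published once the analysis is complete".
- **Delivery of Interventions:** participants who are unwilling, who do not comply, or who "meet any exclusion criteria during the study period are withdrawn from the study". The Exclusion Criteria include pain too severe for conservative treatment and an indication for surgery.
- **Sample Size:** "Furthermore, assuming a 20% attrition rate, the final sample size for this study was 90 participants".

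**The concern.** A robustness check should change the assumption that is in doubt. Here the doubtful assumption is that, given the recorded data, participants who leave would have had the same later pain as comparable participants who stay. Bayesian and regression imputation, in standard form, both start from it. The second can show whether results depend on the form of the imputation model. It cannot show what happens if the missing scores are systematically worse than the recorded data predict.

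The documents make that possibility plausible. The primary outcome is pain, participants know their arm, and someone whose pain comes to meet an exclusion criterion is withdrawn by rule. If such withdrawals are more common, or their unrecorded pain worse, in one arm, both imputations carry the same bias and agree with each other. A reader told that the imputation had been made robust would be wrongly reassured.

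**Working it through.** **The plan's own figures**

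- Completion: 70/90 = 77.8%, as stated. Without final follow-up: 20/90 = 22.2%, against 20% planned.
- Attrition allowance: 72/(1 − 0.20) = 90, as stated.

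**Inputs for the shift calculation**

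- Planned difference of 1 cm and SD 1.36, both from Sample Size; 45 per arm.
- Assumed: 10 missing per arm, and an estimate of 1.0 cm in favour of marma under missing at random.

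**Effect of a shift**

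If missing marma patients are worse than imputed by δ cm, and control patients are as imputed, the difference falls by (missing fraction in the marma arm) × δ = (10/45) × δ = 0.222δ.

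| δ (cm) | Difference (cm) |
|---|---|
| 0 | 1.00 |
| 1 | 0.78 |
| 2 | 0.56 |
| 3 | 0.33 |

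**Where significance is lost**

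SE = 1.36 × √(2/35) = 0.325, held fixed. The smallest significant difference is 1.96 × 0.325 = 0.637. Tipping δ = (1.0 − 0.637)/0.222 = 1.6 cm.

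**Sensitivity to the assumptions**

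- Arm split: with 5 marma and 15 control patients missing, or the reverse, SE = 1.36 × √(1/40 + 1/30) = 0.328 and the threshold is 0.644. Tipping δ = 0.356/(5/45) = 3.2 cm, or 0.356/(15/45) = 1.1 cm.
- SD: an SD of 1.36 gives about 60 evaluable participants, not the stated 72, which would need an SD of about 1.51. With 1.51 and 10 missing per arm, SE = 1.51 × √(2/35) = 0.361, the threshold is 0.707, and tipping δ = 0.293/0.222 = 1.3 cm. The argument does not depend on the 72.

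**Does agreement between the methods reveal the bias?**

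Trials were simulated with 45 per arm, 10 missing per arm, SD 1.36, baseline–outcome correlation 0.5, a completer effect of 1.0, and missing marma patients truly 2 cm worse. The effect over all randomised patients is then 1.0 − 0.222 × 2 = 0.56. A single regression fill returned 1.00 on average, and so did Bayesian-type multiple imputation. The two agree, and both miss the true value by 0.44.

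**Conditional side-effect: a single fill**

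Null trials, same layout, data missing completely at random, imputation from arm and baseline, t test, baseline correlation 0 to 0.7:

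- Deterministic single fill: type I error 13.0% falling to 8.3%.
- One random fill: 10.5% falling to 8.2%.
- Multiple imputation: 5.3% to 4.7%.

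With one interim VAS added to a deterministic fill, the error was roughly 7 to 10%. With ANCOVA after a baseline-only fill it was about 13%. If the fill is single, the range is therefore about 7 to 13%; if it is multiple, about 5%.

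**The case against.** The strongest reply has four parts.

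1. **Pain-related withdrawal is not automatically outside missing at random.** Pain is recorded at every visit. If dropout depends on recorded pain, an imputation model that includes interim VAS handles it; in a check with dropout driven by observed interim pain and a true difference of −1.0, such imputation returned −1.00. This stands. The problem arises only if dropout depends on pain that was not recorded, which the withdrawal rule makes plausible but does not prove.
2. **A reader might infer that the regression step is a single fill that understates the error.** The text does not say so. Stata can run regression imputation as multiple imputation, and then nothing is understated. The step is also secondary and conditional on the data. The inflated error rate is therefore only a conditional remark.
3. **A reader might infer that missing data are never stress-tested.** That goes too far. Two imputation models check dependence on the model, intention-to-treat and per-protocol are both planned, and an analysis plan that is not shown may contain more. What remains is that no analysis stated here varies the missing-at-random assumption: per-protocol leaves people out, and intention-to-treat uses the imputed values.
4. **The 22.2% is not the rate of missing primary outcome.** It concerns the final visit as of November 2025. The primary outcome also includes day 30, where missingness is unknown and may be lower. Completed data cleaning suggests that the 20 are final, but the article does not say so outright.

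The number of imputations and the choice of a mixed model instead are matters for an analysis plan and form no part of this point.

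**Conclusion.** The concern holds in limited form. The article gives a reason for robustness that the second method cannot supply: in standard form both imputations rest on missing at random, and no analysis it describes relaxes this.

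With 10 of 45 missing per arm, each 1 cm of unmodelled worsening in missing marma patients costs 0.22 cm of the difference. An estimate of 1.0 cm stops being significant at about 1.6 cm. Across the splits and SDs tried one at a time, that tipping shift runs from 1.1 to 3.2 cm. These figures rest on an assumed estimate, an assumed arm split, a fixed standard error, and final-visit missingness. The missing-at-random premise is the default for both methods and is not written in the article. The documents do not establish that the dropout is in fact related to unrecorded pain, or that the planned analysis has an inflated error rate.

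**What to change.** In Data Analysis:

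- State that the primary handling of missing VAS is the Bayesian imputation, done as multiple imputation under missing at random, with arm, baseline VAS and interim VAS in the model and results pooled across the imputed sets.
- Remove the claim that regression-based imputation makes this robust. Replace that step, as the robustness check, with a delta-adjusted tipping-point analysis of the VAS outcome: worsen the imputed scores of marma participants without data in steps, and report the shift at which the conclusion changes.
- Report missing VAS by arm at day 30 and at 3 months, so that readers can judge whether the tipping shift is plausible.

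The cost is a few sentences and a little programming. The article says the analysis is not complete, so the change can still be made, and it should be dated and described as made after enrolment ended. The downside is that the result may look less secure.

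### The primary VAS analysis is chosen by the observed data, and the rank-test branch does not address the 1-point mean difference the trial was sized on

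*Protocol article*

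**What the plan says.** All quotes are from the protocol article.

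- **Outcome Measures.** The primary outcome is pain on the VAS, "assessed as the change in the 10 cm VAS score at day 30 and after 3 months from baseline".
- **Sample Size.** The calculation starts from an earlier physiotherapy study with a "mean VAS score for back pain of 3.05 (SD 1.36) points after treatment" and continues: "Assuming a between-group difference of 1 point, with 80% power at 5% level of significance". A mean, an SD and a difference in points describe a difference in means.
- **Data Analysis, first paragraph.** "Between-group comparisons will be performed using the independent-samples" t test or Mann-Whitney, the choice "depending on the normality of the data". No normality check or threshold is named, and no separate analysis is named for the primary outcome.
- **Data Analysis, second paragraph.** Outcomes measured at several time points may be analysed by repeated-measures ANOVA or by Friedman. ANCOVA is used only when the groups are seen to differ at baseline. "A 2-sided significance level of 5% will be considered for all analyses".

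**The concern.** Three choices in the section depend on the data or are left open: t test or Mann-Whitney, repeated-measures ANOVA or Friedman, and ANCOVA or not. All three can reach the primary VAS outcome, because nothing sets that outcome apart.

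The two between-group tests answer different questions. The t test compares means and yields a VAS difference in points with a confidence interval. Mann-Whitney asks whether a participant in one arm tends to rank above one in the other. It corresponds to a mean difference only if the arms differ by a pure shift. If the check points to the rank test, the quantity the trial was sized on is neither tested nor estimated. Day 30 and 3 months could also end up with different tests.

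At stake are a fixed primary hypothesis, an interpretable effect estimate, and some power that baseline VAS could supply.

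**Working it through.** **1. What was sized.** Inputs from Sample Size and Data Analysis: difference 1, SD 1.36, two-sided 5%, power 80%.

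n per arm = 2 × 1.36² × (1.960 + 0.842)² / 1² = 29.03, rounded up to 30, so 60 in total. The exact t calculation gives 31 per arm, 62 in total. The article states 72. The attrition step does reproduce: 72 / 0.8 = 90. The gap between 60 and 72 is a separate matter. What counts here is that the sized quantity is a difference in means, and that a single fixed comparison of means needs no more participants than planned. At 36 per arm its power is 87.7% (86.8% by exact t).

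**2. Behaviour of the two-stage rule.** The article names no normality check and gives no distribution, so both are assumed: Shapiro-Wilk at 5% in either arm, 36 per arm, SD 1.36, 6,000 simulated trials per row. The Monte Carlo standard error near 5% is √(0.05 × 0.95 / 6000), about 0.3 percentage points. Means are equal in every row.

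| Shapes | Rank branch chosen | Two-stage rejects | t test rejects |
|---|---|---|---|
| Normal in both arms | 10.5% | 4.6% | 4.5% |
| Same gamma (shape 2) in both arms | 97.8% | 4.8% | 4.6% |
| Exponential v normal | 99.2% | 9.0% | 5.5% |
| Gamma (shape 2), opposite skew | 97.5% | 16.4% | 5.3% |

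Four further assumed settings, at 35 per arm with equal means and a responder mixture in one arm, gave 6.7% to 16.6% for the two-stage rule and 4.9% to 5.4% for the t test.

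**3. How often the rank branch is taken.** This depends on the variable tested. For raw follow-up VAS drawn from a gamma with mean 3.05 and SD 1.36, at 35 per arm, it is about 67%. For the stated endpoint, change, with that same follow-up distribution and a normal baseline with SD 1.36, it is about 17% at r = 0.3 and 16% at r = 0.5. Rejection is then 5.4% and 5.2%.

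**4. Baseline VAS as a covariate.** Here r is the correlation between baseline and follow-up VAS, which the article does not give. SD is 1.36 at both times, the effect is 1 point, and n = 35 per arm is half of the 70 completers in Results (their split by arm is not reported).

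- SD of change = 1.36 × √(2(1 − r))
- ANCOVA residual SD = 1.36 × √(1 − r²)
- Noncentrality = 1 / (SD × √(2/35)); power from the noncentral t with 68 df (change) or 67 df (ANCOVA)

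| r | SD of change | Power, t test on change | ANCOVA SD | Power, ANCOVA |
|---|---|---|---|---|
| 0.3 | 1.609 | 73% | 1.297 | 89% |
| 0.5 | 1.360 | 86% | 1.178 | 94% |
| 0.7 | 1.053 | 97% | 0.971 | 99% |

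With all 45 per arm, ignoring imputation uncertainty, the figures for change v ANCOVA are 83% v 95% at r = 0.3 and 93% v 98% at r = 0.5.

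**The case against.** **The type I error is held.** A reader might infer that testing normality first inflates the error rate in general. The simulations do not support that: with one distribution in both arms, rejection is 4.6% to 4.8%. The 7% to 17% arises only when treatment changes the shape of the outcome but not its mean, and nothing in the article says this will happen. This part of the objection stands, so the error-rate point is conditional.

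**The rank test can help.** With the same gamma skew in both arms and a true 1-point shift, the two-stage rule had 94.8% power against 87.8% for the t test. That is true under a pure shift, but it does not supply the mean difference. It is a reason to keep the rank test as a sensitivity analysis.

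**Baseline is already used.** A reader might infer that baseline VAS is ignored. It is not: the primary outcome is a change from baseline. What is missing is unconditional adjustment for it as a covariate. The power gain from that is an efficiency argument, separate from the normality rule, and it shrinks to about 1 percentage point at r = 0.7.

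**The article does not call the t/Mann-Whitney rule the primary analysis.** Correct, and repeated-measures ANOVA or Friedman may also apply to VAS. That leaves the primary analysis less fixed, and it means that deleting the normality rule alone would not be enough.

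**A statistical analysis plan may settle this.** It may, but the point concerns rules that the article states.

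**Conclusion.** The concern holds in a limited form. The article lets the observed data choose the primary VAS analysis among several methods, and the rank branch does not address the 1-point mean difference behind the sample size. The main harm is an unfixed hypothesis and effect measure.

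Excess rejection for a mean difference, about 7% to 17% against about 5%, is confined to equal means with differing shapes and rests on assumed distributions and an assumed normality check. The 67% rank-branch frequency should not be read as applying to this endpoint, because it belongs to raw skewed scores. On change scores with a normal baseline it is about 17%; a skewed baseline could alter that.

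The gain from ANCOVA is roughly 16, 8 and 1 to 2 percentage points of power at r = 0.3, 0.5 and 0.7 with 35 per arm, given a common SD of 1.36. The change is worth making because it fixes the target of the analysis and uses data already collected.

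**What to change.** For the primary outcome, replace three provisions together: the normality-dependent choice of test, the repeated-measures ANOVA or Friedman option, and the ANCOVA that waits for an observed baseline difference. Put one analysis in their place:

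- a linear model of VAS on arm and baseline VAS at each primary time point (day 30 and 3 months), whatever the distribution or the observed baseline balance;
- the adjusted mean difference with its 95% CI, using robust or bootstrap standard errors if residuals are skewed;
- Mann-Whitney as a sensitivity analysis only.

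The cost is a wording change and no new data. It is more than an editorial matter, though. The abstract says analysis is ongoing, Results says data cleaning is complete, and the trial is open label, so the change should be dated and made before between-group results are examined. Protocol Amendments requires changes in analysis methods to be reported, with reasons, to the sponsor and the ethics committee.
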